#### **Expected Serious Adverse Reaction**

A serious adverse reaction by its nature, incidence, severity, or outcome is anticipated and identified in the current version of the intervention safety information are classified as a SAR report. SAR reports are reported to the Coordinating Principal Investigator without undue delay for multicentre clinical trials. Serious Adverse Reaction reports must be recorded in the [UNSW Safety Monitoring Register Template](https://research.unsw.edu.au/document/UNSW%20Safety%20Monitoring%20Register%20Template.xlsx).

#### **Suspected Unexpected Serious Adverse Reaction (SUSAR)**

A serious adverse reaction by its nature, incidence, severity, or outcome is unanticipated and not identified in the interventions instructions for use or safety information are classified as a SUSAR.

Fatal or life-threatening Australian SUSAR reports are reported to the Coordinating Principal Investigator, the sponsor's delegate and the approving HREC within 7 calendar days after being made aware of the case follow up information reported within a further 8 calendar days.

All other Australian SUSAR reports are to be reported to the Coordinating Principal Investigator, the sponsor's delegate and the approving HREC within 15 calendar days after being made aware of the case follow up information reported within a further 8 calendar days. SUSAR reports must be recorded in the [UNSW Safety Monitoring Register Template](https://research.unsw.edu.au/document/UNSW%20Safety%20Monitoring%20Register%20Template.xlsx).

1. Significant Safety Issue (SSI)

A safety issue that could adversely affect participants' safety or materially impact the trial's continued ethical acceptability or conduct. The Human Research Ethics Committee and Sponsor's Delegate must be notified of all significant safety issues within 15 calendar days of the sponsor instigating or being made aware of the issue**.** SSI reports must be recorded in the [UNSW Safety Monitoring Register Template](https://research.unsw.edu.au/document/UNSW%20Safety%20Monitoring%20Register%20Template.xlsx).

1. Urgent Safety Measure (USM)

A measure that is taken to eliminate an immediate hazard to a participant's health or safety. Significant safety issues where an urgent safety measure is required to be taken to eliminate an immediate hazard must be classified as a significant safety issue requiring an urgent safety measure. The Human Research Ethics Committee and the Sponsor's Delegate must be notified of any significant safety issues that meet the definition of an urgent safety measure should be notified within 72 hours. Examples include:

- a serious adverse event that could be associated with the trial procedures and that requires modification of the conduct of the trial
- a patient population hazard, such as lack of efficacy of an intervention used for the treatment of a life-threatening disease.

USM reports must be recorded in the [UNSW Safety Monitoring Register Template](https://research.unsw.edu.au/document/UNSW%20Safety%20Monitoring%20Register%20Template.xlsx).

1. Safety Assessment Flow Chart Investigational Medical Product Trials

[figure not shown]

1. Register of Clinical Trial Safety Monitoring Reports

A register of all event reports assessed and classified is to be retained by the Coordinating Principal Investigator and reported to the trial sponsor annually and the HREC if required.

1. Reporting of Clinical Trial Safety Monitoring Reports

Single case reports of Adverse Events Adverse Reactions, Serious Adverse Events (SAEs), Serious Adverse Reactions (SARs), reports do not need to be reported to the UNSW Sponsor's Delegate or the HREC. All single case reports must be recorded in a safety monitoring register and are reported to the UNSW Sponsor's Delegate annually.

#### **Emerging Safety Issues**

The Trial Management Group, Trial Safety Committee or the Data Safety Monitoring Board is responsible for reviewing the safety information to identify any serious emerging safety concerns. If safety concerns are identified, this body will establish a plan to minimise the time participants may be placed at excess risk of harm. Before implementing the plan, the Trial Management Group, Trial Safety Committee or the Data Safety Monitoring Board must seek the advice of the human research ethics committee and sponsor's delegate.

#### **Annual assessment of safety**

The following information must be provided in a report to the sponsors delegate annually:

- Documented evidence that the Trial Management Group, Trial Safety Committee, or the Data Safety Monitoring Board (e.g. meeting minutes) confirmed that regular safety reviews occurred.
- Analysis of the trial intervention(s) and its implications for participants considering all available safety data and relevant clinical or non-clinical studies results.
- Any reports of emerging safety issues and a description of any measures taken or proposed to minimise risks.
- A copy of the safety monitoring register.

# **Non-compliance, Protocol Deviation and Serious Breaches of Good Clinical Practice**

## **Protocol Deviation**

A protocol deviation is defined as any breach, divergence or departure from the requirements of Good Clinical Practice, the clinical trial protocol, the clinical trial standard operating procedures, or the human ethics approval that does not have a significant impact on the continued safety or rights of participants or the reliability and robustness of the data generated in the research or clinical trial. Protocol deviations are events that do not occur persistently or systematically and do not potentially result in participant harms. Examples of protocol deviations include but are not limited to:

- Deviations because of participant adherence to the protocol, including rescheduled study visits, participants refusal to complete scheduled research activities or failure to complete self-report questionnaires required by the study protocol.
- Blood samples obtained or clinical trial testing occurring at times close to, but not precisely at the time points specified in the protocol.
- The completion of consent forms, safety monitoring report, case report forms or data collection tools in a manner that is not consistent with the protocol instructions or failure to make reports within the required reporting timeframes.
- Administration of the clinical trial investigational medical product or device in a manner that is not consistent with the manufacturer's instructions for use.
- Use of an unapproved version of the participant information statement or recruitment of participants using unapproved recruitment procedures.
- Inclusion of a participant that does not meet the inclusion criteria.
- An urgent safety measure must be taken to eliminate an immediate hazard to a participant's health or safety.

## **Serious Breach of Good Clinical Practice**

A serious breach is defined as a breach of Good Clinical Practice, the clinical trial protocol, the clinical trial standard operating procedures, or the human ethics approval that is likely to affect to a significant degree the safety or rights of participants or the reliability and robustness of the data generated in the clinical trial. Examples of serious breaches include but are not limited to:

- Persistent or systematic non-compliance with the instructions for completing consent forms, safety monitoring forms, case report forms or data collection tools that result in continued missed or incomplete data collection.
- Failure to record or report adverse events, serious adverse events, suspected unexpected serious adverse reactions, significant safety issues where urgent safety measures were implemented.
- Failure to conduct clinical trial procedures following the clinical trial delegation log.
- Widespread and uncontrolled use of protocol waivers affecting eligibility criteria, which leads to harm to trial subjects.
- Failure to report investigational medical product or device defects to the clinical trial sponsor or any relevant regulatory body.
- Failure to conduct research following the issued approvals, permits or licences by required laws, regulations, disciplinary standards, and UNSW policies relating to the responsible or safe conduct of research.
- Concealing or facilitating breaches (or potential breaches) of the Research Code by others.
- Researching without the requisite approvals, permits or licences required by laws, regulations, disciplinary standards, and UNSW policies related to the responsible or safe conduct of research.
- Failure to conduct research as approved by an ethics review body where that conduct leads to (or has the potential to) results in participant harms.
- Researching without ethics approval as required by the National Statement on Ethical Conduct in Human Research where that conduct leads to (or has the potential to) result in participant harms.
- Any breaches as outlined in the UNSW Research Misconduct Procedure or the Australian Code for responsible conduct of research that leads to (or can potentially) result in participant harms.

## **Reporting Protocol Deviations**

- Protocol deviations occurring at a site must be documented in site files and reported by the principal site investigator to the Coordinating Principal Investigator.
- The Coordinating Principal Investigator must review the protocol deviation and the clinical trial protocol to establish the corrective actions and preventative steps to prevent the deviation from reoccurring.
- The protocol deviation and corrective action plan must be reported to the UNSW Sponsor's Delegate by the Coordinating Principal Investigator or Coordinating Research Team using the protocol deviation report form.

## **Reporting of a Serious Breach**

- The Principal Investigator must report a serious breach occurring at a participating site to the Coordinating Principal Investigator within a specified timeframe.
- The Coordinating Principal Investigator must review the serious breach, along with the clinical trial protocol, to develop a Corrective and Preventive Action (CAPA) that defines the steps to prevent the serious breach from reoccurring.
- The serious breach report and the CAPA must be provided to the approving HREC, and the UNSW sponsors delegate for review and approval.

## **Reporting of Serious Breaches by Third Parties**

- A Suspected Breach is a report judged by the reporter as a possible serious breach but has yet to be formally confirmed as a serious breach by the sponsor.
- A Suspected Breach form must be completed when a third party (e.g., individual/institution) wishes to report a suspected breach of Good Clinical Practice or the protocol and should be reported directly to the reviewing HREC without reporting through the sponsor.
- Recording of Protocol Deviation and Serious Breach Reports
- A register of protocol deviation and serious breach reports must be recorded. Written records and copies of documentation sent to the sponsor must be retained in the Investigator Site File.
- Copies of protocol deviation and serious breach reports must be recorded, written records and copies of documentation sent to the sponsor, referrals made to the HREC or establishing whether a breach of the Australian Code for Responsible conduct of research must be retained in the Master Site File.

# **Review of a Protocol Deviation and a Serious Breach**

- The UNSW Sponsor's Delegate will review reports to establish whether the event meets the definition of a protocol deviation or serious breach,  establish whether the proposed CAPA is appropriate and establish whether there is or will be ongoing impact reliability and robustness of the data generated.
- The UNSW Sponsor's Delegate will seek advice from the approving HREC on the corrective and preventive actions.
- Protocol deviation or serious breach reports where a UNSW researcher, staff or student is responsible for the protocol deviation or the serious breach will be reviewed as per the [UNSW Research Misconduct Procedure](https://www.gs.unsw.edu.au/policy/documents/researchmisconductproc.pdf) to establish a breach of the [UNSW Research Code of Conduct](https://www.gs.unsw.edu.au/policy/documents/researchcode.pdf) has occurred.
- Protocol deviation or serious breach reports where the UNSW Sponsor's Delegate determines that site personnel are responsible for a protocol deviation or the serious breach will be referred onto their responsible institution for review under their Research Misconduct procedures to establish whether a breach of the [Australian Research Code for the Responsible Conduct of Research](https://www.nhmrc.gov.au/about-us/publications/australian-code-responsible-conduct-research-2018) has occurred.

# **Statistics**

Data collected throughout the study will be analysed using hierarchical linear modelling or linear mixed models. Both intention-to-treat analysis (ITT; using all randomised participants) and completers’ (PP) analysis will be used.

Primary study parameters:

The main conclusion for study aim 1 (testing the efficacy of the DWM intervention, according to K10 scores) will be based on the ITT analysis of the primary outcome. A secondary analysis of the primary outcome will also be presented using the PP population. To estimate the treatment effect, data from Structured Assessments 1-4 will be used. A linear mixed model will be employed for the primary endpoint analysis, which will have treatment as fixed effects, baseline measurement of primary endpoint as covariate, and subject as random effects. The mean difference between two treatment arms at each visit/time together with its 95% confidence interval will be derived from the mixed model. Covariate-adjusted mixed model of primary endpoint will also be performed by adding pre-specified covariates at baseline (gender, age, education, traumatic experiences, and severity of symptoms) into the above model.

- Secondary study parameters: A linear mixed model as mentioned for the primary outcome analysis will be carried out for analysing the secondary outcomes (e.g., PTSD, Suicidal Ideation, Self-Identified Problems, Wellbeing, Functional Impairment, Digital Markers).

The main conclusion for study aim 2 (testing the mechanisms of change within the DWM intervention) will be based on the PP analysis, to ensure that only data from participants who received a sufficient ‘dose’ of the intervention are analysed. Cross-lagged panel analysis will be used to determine the temporal sequencing of psychological factors over the course of the intervention period, to test whether the hypothesised processes were mechanisms of change driving the intervention effects [hypothesis 2].

- The hypothesised mechanisms are: psychological flexibility (primary), emotion regulation, social satisfaction and functioning, and intolerance of uncertainty.

Missing data: Missing data will be treated as missing at random (MAR). No imputations of missing values will be made, as multilevel models can deal with missing data (Singer & Willett, 2003).

Other study parameters:

- Treatment fidelity: In order to determine whether the intervention-as-implemented does not differ from the intervention-as-designed, fidelity checklists filled out by research assistants independent to the treatment facilitation team will be completed for a random sample, stratified on facilitator, of sessions/participants. Treatment fidelity will be analysed as a manipulation check.

Interim analysis (if applicable): Interim analyses will be considered in case safety issues are (suspected to be) violated.

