**Primary endpoint:**

This study will implement a waitlist control Randomised Controlled Trial design, where participants will be randomly assigned to active treatment (DWM) or a waitlist control condition (WL) on a 2:1 ratio.

The main study parameter will be psychological distress, measured using the Kessler Psychological Distress Scale – 10-item version (K10; Kessler et al., 2002). A description of this measure can be found under “Measurement Instruments”. This measure is administered at pre-treatment (including as a screening measure), mid-treatment, immediately post-treatment, and 1 month after the completion of treatment.

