# **Sample Size**

We plan to enrol 303 participants into the trial. As a key focus of this study is to investigate psychological and social mechanisms underlying the impact of DWM on mental health outcomes, we will implement a 2:1 allocation ratio (DWM to WLC) to ensure analyses are adequately powered. Based on previous research, we aim to detect a medium between-groups effect size (0.40) (Tol et al., 2020; Acarturk et al., 2020) on our main outcome measure (Kessler-10). With alpha of 0.05 and power of 80%, we will need to include a minimum of 224 participants across both arms (150 in the DWM arm and 73 in the WLC). We estimate 35% attrition given the mobile nature of the refugee population in Indonesia, and thus we will need to recruit 303 participants into the trial.

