Participants deemed eligible based on the online screener and phone screener process will be invited to participate in the trial and sent a link to review the trial’s Participant Information Statement and Consent Form. Following informed consent, participants will be contacted to book their first assessment (Structured Assessment 1). Structured Assessments will be conducted by trained research assistants called ‘Assessors’ (see ‘Trial Personnel’ below) and will involve the administration of the scales in a structured interview format to assess mental health and psychosocial functioning (see ‘Measurement Instruments’ below). If, at the time of the baseline assessment (Structured Assessment 1), the participant’s symptoms of psychological distress have spontaneously improved such that they no longer score above the cut-off, they will be provided feedback on their test outcomes and it will be explained why they are no longer eligible for the study.

After the baseline assessment, participants will be randomized on a 2:1 (active treatment : waitlist control) basis by an independent research assistant, not involved in the assessments, using computerized software. Participants will be randomised to either the Active Treatment condition (*n*=214) or the Waitlist Control condition (*n*=107) to form a single-blind waitlist control RCT design. Participants in the Active Treatment condition will receive the 5-week DWM intervention from Weeks 1-5. Regardless of condition, all participants will complete Structured Assessments every 3 weeks.Upon completion of the final Structured Assessment (1-month follow-up, conducted 9-weeks following baseline assessment), participants in the Waitlist Control condition will gain access to the DWM workbook and audio files.

The instruments administered in Structured Assessments 2-4 closely resemble those used in Structured Assessment 1, with minor changes (as some scales do not need to be re-administered). This is outlined in the ‘Measurement Instruments’ section below. In case participants do not attend a scheduled assessment, the research team will attempt to contact them via follow-up text messages and/or phone calls for a maximum of eight times for scheduling a new appointment.

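### The primary K10 model has no visit or treatment-by-visit term, so it cannot give the per-visit differences promised from it, and the text leaves open whether the baseline is also an outcome

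*Protocol*

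**What the plan says.** All of the model text is in the protocol's section 14 (Statistics), under the primary study parameters.

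- Data: "To estimate the treatment effect, data from Structured Assessments 1-4 will be used".
- Terms of the model: "which will have treatment as fixed effects, baseline measurement of primary endpoint as covariate, and subject as random effects".
- Output: "The mean difference between two treatment arms at each visit/time together with its 95% confidence interval will be derived from the mixed model".
- The covariate-adjusted version adds baseline characteristics to this model and changes nothing else.
- Secondary outcomes: "A linear mixed model as mentioned for the primary outcome analysis will be carried out for analysing the secondary outcomes". Digital markers are among the examples listed.

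Two other places fix the timing. The primary endpoint text says of the K10: "This measure is administered at pre-treatment (including as a screening measure), mid-treatment, immediately post-treatment, and 1 month after the completion of treatment". The trial intervention text in section 10 places randomisation after Structured Assessment 1: "After the baseline assessment, participants will be randomized on a 2:1 (active treatment : waitlist control) basis". Under the measurement table, a footnote restricts digital markers to Assessments 1 and 3.

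**The concern.** There are two linked defects.

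First, the listed terms and the promised output do not fit together. The fixed part of the model contains treatment and baseline K10 only. It has no term through which the arm difference could vary by visit.

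Second, the wording permits the baseline K10 to enter twice, once as an outcome row and once as the covariate. Because Assessment 1 precedes randomisation, its expected arm difference is zero. An outcome row at that visit carries no treatment effect and is fully known from its own covariate.

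This model carries the main Aim 1 conclusion and is reused for the secondary outcomes. Two competent analysts following the same text could report different headline effects and different intervals, and neither could be said to have departed from the protocol.

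**Working it through.** **Inputs from the protocol.** Four K10 visits, with Assessment 1 before randomisation; model terms as listed; standardised effect 0.40; 2:1 allocation; 35% attrition; 303 enrolled (202:101 at 2:1). **Assumed, not in the protocol:** standardised SD 1, equal correlation between visits (0.3 to 0.8 across the checks), the effect profiles, a common time trend, and the way dropout builds up.

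**The plan's own figure.** Section 8 states: "With alpha of 0.05 and power of 80%, we will need to include a minimum of 224 participants across both arms". For two means at 2:1, two-sided, the control arm needs (1 + 1/2)(1.96 + 0.84)² / 0.40² = 73.5, rounded up to 74. The active arm is then 148 and the total 222. The t-test version gives 222.7. The stated 224 is reproduced closely, so 0.40 is a fair reference effect.

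**Step 1: the contradiction.** The mean model is E(Y) = a + b·treatment + c·baseline. The arm difference at any visit is b. A separate difference at each visit needs a treatment-by-visit term, and the model lists none.

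**Step 2: Assessment 1 as outcome and covariate, effect pooled.** Every regressor is constant within a participant. With complete data, the random-intercept estimate therefore equals ordinary regression of the participant's mean, (Y1+Y2+Y3+Y4)/4, on treatment and Y1. Given Y1, treatment explains nothing further in Y1. Writing d2, d3 and d4 for the later differences:

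b = (0 + d2 + d3 + d4)/4 = 0.75 × mean(d2, d3, d4).

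| True effect at Assessments 2/3/4 | Mean of the three | Pooled b | b against Assessment 3 | b against Assessment 4 |
|---|---|---|---|---|
| 0.4/0.4/0.4 | 0.40 | 0.30 | 25% below | 25% below |
| 0.2/0.4/0.4 | 0.333 | 0.25 | 37.5% below | 37.5% below |
| 0.2/0.4/0.2 | 0.267 | 0.20 | 50% below | equal |
| 0.4/0.3/0.2 | 0.30 | 0.225 | 25% below | 12.5% above |

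REML simulation (224 participants, correlation 0.6, 400 runs per profile) returned 0.304, 0.249, 0.202 and 0.226.

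With 303 participants and dropout spread evenly over the three later visits to reach 35%, a constant 0.40 came out as 0.269, and 1 − 0.269/0.40 = 33%. Dropout raises the weight of the baseline row.

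**Step 3: test and power under that reading.** With complete data the standard error also shrinks by 0.75, so the test statistic is unchanged. For 0.2/0.4/0.4 the literal model and the same model on Assessments 2-4 both rejected in 97.8% of runs.

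**Step 4: Assessment 1 as outcome and covariate, with visit and treatment-by-visit added.** The pooled dilution disappears. However, the Assessment 1 rows are almost fully explained by their own covariate. They pull down the residual variance that the model shares across visits, so per-visit standard errors are about 10-13% too small. Simulation under no effect (202:101, complete data, random intercept, one baseline slope, 8,000 runs) gave type I error at Assessment 3 of 7.3%, 7.9% and 8.5% for correlations 0.3, 0.5 and 0.7. With Assessments 2-4 as outcomes it was 5.0-5.1%. As a plausibility check, 1.96 × 0.89 = 1.74, and the two-sided normal tail beyond 1.74 is about 8%.

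**Step 5: Assessment 1 as covariate only.** There is no dilution. With visit and treatment-by-visit added, a true 0.40 at each visit was recovered (0.403, 0.401, 0.411). Without them the model averages Assessments 2-4, and Step 1 still applies.

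**Step 6: digital markers.** There are two measurements, at Assessments 1 and 3. If Assessment 1 is covariate only, each participant has one outcome row, and a random subject effect cannot be separated from residual error. If it is also an outcome row, the pooled coefficient is (0 + d3)/2, half the Assessment 3 effect.

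**The case against.** The strongest reply is that the protocol never says Assessment 1 is a response. It says that the data from Assessments 1-4 are used and then assigns the baseline the role of covariate. Assessment 1 as covariate with Assessments 2-4 as outcomes satisfies both sentences and is a standard analysis. The promised per-visit output also implies that a treatment-by-visit term was intended, in which case no pooled coefficient would be reported. Visit coding and covariance structure are commonly left to a SAP.

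Much of this stands. A reader might infer that the protocol does use the baseline as an outcome and so understates the effect by at least 25%. The text does not support that. The dilution needs an Assessment 1 outcome row and a pooled effect together. Even then, 25% is exact only against the mean post-baseline effect with complete data. Against the 1-month follow-up it can be zero, or reversed if the effect wanes.

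A reader might also infer a loss of power, for instance by putting 0.30 with SD 1 into the sample-size formula, which gives 55.7% at 150 and 73 per arm. That is wrong, because estimate and standard error shrink together.

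What does not stand is treating the matter as mere SAP detail. The protocol does not leave the model open. It lists the terms and then states an output that those terms cannot produce. Inferring the missing interaction does not settle the role of Assessment 1, and with a random intercept the double use then costs type I error (Step 4).

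**Conclusion.** The point holds in a limited form. The model as listed cannot give the promised per-visit differences; this follows from its terms and needs no assumption. The role of Assessment 1 is ambiguous, and the consequence depends on how that is resolved:

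- **Outcome and covariate, effect pooled:** the coefficient is 25% below the mean post-baseline effect with complete data, and about a third below under the assumed dropout path to 35% with a constant effect. The test keeps its level and, with complete data, its power. The estimate and its interval describe no post-treatment time point.
- **Outcome and covariate, treatment-by-visit added, random intercept:** no dilution, but per-visit standard errors are about 10-13% too small and type I error at Assessment 3 is about 7-9%, assuming correlation 0.3-0.7 and complete data.
- **Covariate only:** no dilution and no inflation, but the contradiction over per-visit differences remains.

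The contradiction is certain. The numerical consequences are conditional, and the protocol does not say which case applies.

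**What to change.** Rewrite the model sentence in section 14 in one of two ways.

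1. Outcome: K10 at Assessments 2, 3 and 4. Fixed effects: treatment, visit (categorical), treatment-by-visit and baseline K10, with Assessment 1 serving as covariate only. Within-participant correlation is modelled as now intended. Participants with no later assessment contribute no outcome row.
2. Outcome: K10 at Assessments 1 to 4, with visit and treatment-by-visit terms, a baseline mean constrained to be common to both arms, and no baseline covariate. This keeps every randomised participant with a baseline in the ITT likelihood.

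Do not combine the two. In either case, name the visit whose treatment contrast carries the Aim 1 conclusion.

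Use the same form for secondary outcomes measured at all four assessments. For digital markers, regress the Assessment 3 value on treatment and the Assessment 1 value, without a random subject effect. A baseline-by-visit term and the choice of covariance structure are optional.

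The cost is a few sentences of text. No data collection, visit or sample-size change is involved.
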